### Process evaluation

#### Quantitative

To understand the intervention’s mechanism of change, we will survey participating clinicians in both groups prior to intervention delivery and again 12 months later to measure theoretical constructs targeted by our intervention and changes in these constructs associated with the intervention [38]. We will assess constructs based on models and measures from the iQuaD study including constructs from social cognitive theory (intention, self-efficacy, outcome expectancies), volitional constructs (action planning, coping planning) and behavioural automaticity for each of the six targeted clinical behaviours. In addition, we will also investigate whether the intervention alters perceptions of goal facilitation, goal conflict and goal priority between clinical behaviours based on recently developed short measures [29], as well as measures of clinicians’ time usage. Finally, given the team-based nature of primary care diabetes management we will explore whether the intervention alters any perceptions of team climate (participation, support for innovation, vision, and task orientation).

#### Qualitative

There will be two qualitative components to the study. First, a preliminary set of interviews will be conducted with a convenience sample of GPs and nurses to assess perceived barriers and facilitators to engaging in each of the six target behaviours. The results of this work will help to inform the development of the quantitative questionnaires. The interviews will also involve assessing preferences for how interventions might be delivered in a feasible and accommodating way and findings will serve to further inform development of intervention content and delivery. Second, after the delivery of the intervention we will conduct an interview study with GPs and nurses in a sample of four practices receiving the intervention to assess perceived intrapersonal, interpersonal, contextual barriers and facilitators to engaging with the intervention sessions themselves, subsequent perceived changes in practice, and usage of the intervention materials. These interviews will also serve to inform the intervention fidelity assessment. Given that interviews involve a time burden and may constitute a co-intervention involving prompting, we will conduct the interviews after the follow-up outcome data has been collected.

### Economic evaluation

The economic evaluation will comprise a cost analysis. All costs will be expressed in 2012/2013 values. The costs of delivering the intervention will be collected. Two main sources will be used to assign costs to healthcare resources [39,40] supplemented when necessary with unit cost data from other official sources and local surveys. Drug costs will be taken from the British National Formulary [41]. Within the trial a questionnaire at 12-month follow-up of an anonymous random sample of 100 patients from each practice will be asked to report on the use of NHS (National Health Service) services and medications over a twelve-month period. No discounting will be applied. A simplifying assumption will be made that the use of all costs and resources occurred at the beginning of the period. Specifically, the economic evaluation will involve the following:

1. Assessment of the costs of delivering the intervention in terms of staff training costs (both facilitator costs and GP time used in training) and any increase in the amount of standard patient education leaflets used by practices.

2. The average cost per patient to the NHS of medications prescribed in relation to hypertension, glycaemic control, and weight control. Conditional on available data, typical medication costs/usage across the intervention group will be compared to the general population. Differences between control and intervention groups will also be explored.

3. Costs of service usage: using self-reported questionnaires at 12 months from an anonymous sample of patients with type 2 diabetes from each participating practice, we will seek information on the use and NHS cost of community based weight control interventions. We will also seek to use practice records to assess the annual use of diabetes related services within practices. We will explore the use of comparator data that would allow us to forecast the additional workload that a practice would face as a result of successfully changing clinical behaviour and any induced change in patient uptake of practice based diabetes related services. Intervention and control groups will be compared, additionally national level data on service use by diabetes patients will be utilised for an additional comparator group.

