### Objectives

1. Recruit 44 general practices in the North East of England.

2. Develop the content and decide the method of delivery of a multi-faceted, targeted, theory-based intervention to change healthcare professional practice, targeting six key clinical behaviours that currently show room for improvement.

3. Deliver the intervention to GPs and nurses in 22 general practices.

4. Collect outcome data on the six behaviours by a combination of patient survey and computer data extraction 12 months after intervention delivery.

5. Collect process data on the six behaviours using semi-structured interviews (analysed qualitatively) and theory-based questionnaires (analysed quantitatively).

6. Assess the fidelity of delivery of the intervention.

7. Conduct a cost analysis using data on the cost of delivering the intervention and cost of healthcare resources used because of the intervention.

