### Recruitment

#### Step one: general practice recruitment

Potential participating clusters (*i.e.*, general practices) will be invited to participate by research facilitators who will identify a practice contact as a primary point of contact for the research team. The study research associate (RA) will also present the study design at local GP research forums to garner interest. Once identified, the study RA will contact practices to obtain written practice-level agreement to participate in the trial in principle and to subsequently arrange details of attendance of GPs, nurses and healthcare assistants at the intervention delivery sessions.

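### The delivery costing names facilitator and GP time only, although nurses receive the intervention and healthcare assistants' attendance is also arranged, so delivery cost is understated

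*Protocol article*

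**What the plan says.** Objective 7 of the protocol article has two parts: "cost of delivering the intervention and cost of healthcare resources used because of the intervention".

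The Economic evaluation section opens its account of the first part broadly: "The costs of delivering the intervention will be collected". Its numbered list then becomes specific. Item 1 assesses delivery cost through "staff training costs (both facilitator costs and GP time used in training"). The only other component that it lists is patient leaflets: "any increase in the amount of standard patient education leaflets used by practices".

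On who receives the intervention:

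- The Aims name GPs and practice nurses or nurse practitioners as the target.
- Objective 3 reads "Deliver the intervention to GPs and nurses in 22 general practices".
- Step one of Recruitment has the research associate arrange "attendance of GPs, nurses and healthcare assistants at the intervention delivery sessions".
- The Participants section counts healthcare assistants among the primary study participants.

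On medication cost, item 2 says that, if data allow, "typical medication costs/usage across the intervention group will be compared to the general population". The next sentence adds that differences between the two trial arms will be explored as well.

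**The concern.** The staff groups in the costing do not match the staff groups who give up time for the sessions. Nurses are a named target of the intervention, and healthcare assistants are expected at the sessions, yet neither group's time appears in item 1. Clinician time spent in a session is a cost to the practice whatever the clinician's role.

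At stake is the delivery-cost half of objective 7. The Discussion says that the cost analysis will inform scalability, for example into continuing medical education. A planner who takes the reported figure as the cost of running the programme would budget too little, because part of the staff time would be missing. The six primary outcomes and their analysis are not affected.

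There is a smaller point in item 2. The general-population comparison comes first and is stated as something that will be done. The randomised comparison comes second and is only to be explored. Of the two, only the randomised comparison bears on the other half of objective 7, "cost of healthcare resources used because of the intervention".

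**Working it through.** The article reports no delivery cost, so there is no figure to reproduce. The check is a comparison of the texts.

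**Step 1: who attends and who is costed**

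| Staff group | Targeted or attending | Named in item 1 |
|---|---|---|
| Facilitators | Deliver the sessions | Yes |
| GPs | Aims; objective 3; Recruitment step one | Yes |
| Nurses | Aims; objective 3; Recruitment step one | No |
| Healthcare assistants | Recruitment step one | No |

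The evidence is strongest for nurses, who appear in all three places. For healthcare assistants it rests on the recruitment step; the Aims and objective 3 do not mention them.

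**Step 2: is the list in item 1 closed?** The parenthesis joins two components with *both ... and*, and it is introduced as the specific content of the evaluation. It reads as complete. Leaflets are the only other component, and they are not staff time.

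**Step 3: direction.** Write F for facilitator cost, L for leaflets, G for GP time cost and N for the time cost of nurses and healthcare assistants.

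- Cost as written: F + L + G
- Full cost: F + L + G + N
- Shortfall: N, which is above zero whenever any nurse or healthcare assistant attends

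**Step 4: size.** The shortfall as a share of full delivery cost is N / (F + L + G + N). The article gives none of these four terms.

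A narrower quantity is the share missing from attendees' time cost alone. Let s be the share of attendee hours that comes from nurses and healthcare assistants, and r their hourly cost relative to a GP. The missing share is s × r / ((1 − s) + s × r). Two sets of values, both assumed and neither from the article, give:

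- s = 0.3, r = 0.3: 0.09 / (0.70 + 0.09) = 0.09 / 0.79, about 11%
- s = 0.6, r = 0.5: 0.30 / (0.40 + 0.30) = 0.30 / 0.70, about 43%

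These are not estimates. They show how far the answer moves with the assumptions. They also exceed the share missing from total delivery cost, because F and L are left out of the denominator.

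**Step 5: the cost comparators**

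| Place | Comparison planned |
|---|---|
| Economic evaluation, item 2 (medication) | General population, conditional on data; intervention versus control, explored |
| Economic evaluation, item 3 (service use) | Intervention versus control; national data on diabetes patients as an additional comparator |
| Cost analysis (prescribing) | Intervention versus control, explored; no general-population comparison named |

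The randomised comparison is present in all three places. Item 2 differs from item 3 in order and emphasis.

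**The case against.** The strongest reply is that this is one parenthesis in a condensed article. The sentence that opens the section, on collecting delivery costs, excludes no staff group, and the investigators may well intend to cost everyone's time. The Cost analysis section draws on questionnaire responses from practices, which could supply it. The error is also confined to a secondary cost description.

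Part of this stands. The intention may be sound, and the point is modest. But the article does not leave the components to a fuller document. It lists them, and the list disagrees with its own account of who takes part. An analyst who follows item 1 would leave nurses out.

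It is also fair to object that no percentage can be defended. That stands in full: team mix and pay would have to be assumed, so only the direction is established.

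A reader might infer something stronger from item 2: that by comparing drug costs with the general population, the plan cannot show what was used because of the intervention, or would charge the cost of having diabetes to the intervention. The documents do not support this. Items 2 and 3 and the Cost analysis section all plan a comparison between the randomised arms. The general-population comparison depends on data being available, and nothing says that its difference will be attributed to the intervention. Missing staff time does not support that inference either, since it affects delivery cost and not resource use.

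**Conclusion.** The point holds for delivery cost. Item 1 counts facilitator and GP time and leaflets, and omits the time of nurses, who are a stated target of the intervention, and of healthcare assistants, whose attendance is arranged. Applied as written, it understates the delivery cost required by objective 7.

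The conclusion rests on two things: that the parenthesis is a complete list of staff time, which is its natural reading, and that at least some nurses or healthcare assistants attend, which the article plans for. The size is unknown and cannot be derived from the article.

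The medication-cost comparator is a minor matter of wording. The right comparison is already in the plan but is placed second.

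**What to change.** In item 1, replace the parenthesis with: facilitator costs and the time of all attending GPs, nurses and healthcare assistants, costed by role from session attendance.

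This needs an attendance log by role. It could be added to the facilitator report that is already completed after each session, and it should be in place before delivery starts, since attendance by role is hard to reconstruct later. The other consequence is a somewhat higher stated delivery cost.

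In item 2, name the intervention-versus-control comparison as the main medication-cost comparison and label any general-population comparison as context only. This costs a change of wording and brings item 2 into line with item 3.

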### Sample size

Practice-level: 44 practices. Individual-level: The study is powered to detect change in the primary outcomes (six different clinical behaviours) between intervention and control practices. For advising behaviours, the primary outcome measure will be patients’ reports of having received the specific behaviours. In this respect, a random sample of 100 patients with type 2 diabetes in each practice will be surveyed. For prescribing and examining behaviours, data will be extracted from the patient computer records of all patients with type 2 diabetes in each practice. Based on our previous study an intra-cluster correlation coefficient (ICC) of 0.06 is expected and to detect a 15% absolute improvement in any of our measures of behaviour (conservatively calculated as 42.5% to 57.5%) with 80% power and 5% significance, our primary and conservative sample size estimate is that we will need 20 patients from a total of 40 practices. As this sample size does not account for any potential loss to follow-up, we will recruit a further four practices (44 in total). Accordingly, two groups of 22 practices will provide us with 83.9% power to detect a 15% improvement in any behavioural outcome. Our previous study (iQuaD) has demonstrated that this level of recruitment at the patient level is achievable, as we received postal outcome data from a mean of 41 patients per practice (having invited 100) and extracted prescribing data on all patients with type 2 diabetes in the practice (from analysing these data we identified that about 20 patients per practice were eligible for the specified prescribing behaviours). Based on our previous study we anticipate a mean sample size of 40 patients per practice and will thus have greater power. Assuming 40 practices (two groups of 20), we would have 89% power to detect a difference of 15 percentage points (42.5% versus 57.5%) assuming a type 1 error rate of 5% and an ICC of 0.06; retaining all 44 practices would increase power to 92%.

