**5.** Over the past 12 months **prescribe additional antihypertensive** drugs for patients with type 2 diabetes whose blood pressure is 5 mmHg above target of 140 mmHg (systolic) or 80 mmHg (diastolic) even following previous management	Received by 40% whose blood pressure (BP) is above a target of 140 mm Hg for Systolic BP or 80 mm Hg for Diastolic BP, even following previous management (via practice-held prescribing data)	QS5 - ‘People with diabetes agree with their healthcare professional to start, review and stop medications to lower blood glucose, blood pressure and blood lipids in accordance with NICE guidance’
**6.** Over the past 12 months **examined foot** circulation and sensation in the feet of patients with type 2 diabetes	Received by 91% of patients (via patient survey)	QS10 - ‘People with diabetes at risk of foot ulceration receive regular review by a foot protection team in accordance with NICE guidance’
		QS11 - ‘People with diabetes with a foot problem requiring urgent medical attention are referred to and treated by a multidisciplinary foot care team within 24 hours’

^a^From NICE quality standard for diabetes in adults (http://www.nice.org.uk/media/7F8/B2/DiabetesQualityStandard.pdf).

Note. QOF = Quality and Outcomes Framework.

Our results showed that in primary care, individual healthcare professionals’ beliefs about these behaviours predicted their clinical behaviour while their perceptions about their workplace did not; multilevel models also showed that variability was primarily between individual clinicians within general practices rather than between the practices [10]. Based on these findings, an intervention targeting individuals within organisations rather than targeting their organisation may be more likely to be effective.

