#### Multiple comparisons

Each of the six individual behaviours will be analysed separately; for each behaviour, we will generate a 95% confidence interval for the effect of the intervention. The 95% confidence interval corresponds to a type 1 error rate of 5%. If we assume that the behaviours are independent, with six separate tests, the probability that one or more is significant at the five percent level is 0.265. Thus the effective type 1 error rate is 26.5% rather than the nominal 5% assumed in the power calculation. However, the probability of two or more tests being significant purely by chance is 0.033. In practice, the behaviours and associated tests are not independent but this figure can be used as a guide. Provided that the intervention is shown to have beneficial effects on at least two of the clinical behaviours this can be regarded as evidence that the proposed method can be used to develop effective interventions.

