## Discussion

This multi-site cluster trial reflects on-going development of an intervention consistent with UK Medical Research Council guidance on the development and evaluation of complex interventions. Despite policy initiatives such as the QOF, there remain gaps in care. The present intervention is novel in its acknowledgement and consideration of multiple behaviour change in clinicians, building on considerable development work. In so doing, it will address important and relevant questions concerning the need to move beyond an isolated focus on changing one behaviour towards a more comprehensive approach that seeks to not only change multiple behaviours, but also to understand the mechanisms underpinning multiple behaviour change. To achieve this, we propose a comprehensive evaluation including not only the main trial analysis focusing on primary endpoints, but also hypothesised pathways/mechanisms of action using behaviour change techniques; intervention fidelity to allow clearer understanding of whether interventions were consistently delivered as designed and if not, why not; theory-based quantitative process evaluation investigating change in targeted hypothesised pathways; qualitative investigation of barriers and facilitators to trial participation; and a cost analysis that will inform scalability (*e.g.* into continuing medical education). The fidelity study will be key to the interpretation of the trial findings and will also identify where intervention delivery can be improved if necessary. Such extended evaluation is consistent with forthcoming MRC guidance on process evaluation.

The study will capture a breadth of key recommended behaviours in diabetes management including prescribing, advising, and examining behaviours. While descriptively involving different types of activities, our intervention will involve targeting constructs that were consistent predictors across multiple clinical behaviours. We do not have any pre-conceived hypotheses concerning which or how many of the six targeted clinical behaviours will change, though we suggest that a positive trial will be defined as change in at least two of the six target behaviours. Of the six behaviours, foot examination was previously shown to be performed at a relatively high (though not optimal) rate and thus may be more challenging to show improvement, though we do still expect to change this behaviour.

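### The 83.9% power for a 15-point gain is claimed for every primary behaviour, but at the only rate the protocol gives for foot examination (91%) that gain cannot occur

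*Protocol article*

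**What the plan says.** The Sample size section presents the trial as powered for all six primary behaviours. It sets the target as "to detect a 15% absolute improvement in any of our measures of behaviour", "conservatively calculated as 42.5% to 57.5" per cent, "with 80% power and 5% significance", where an "intra-cluster correlation coefficient (ICC) of 0.06 is expected". This leads to 20 patients in each of 40 practices. Four more practices are added for loss, after which "two groups of 22 practices will provide us with 83.9% power to detect a 15% improvement in any behavioural outcome". With a mean of 40 patients per practice, the section gives 89% power for 40 practices and 92% for 44.

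Foot examination is the sixth primary outcome in Table 2, measured from practice computer data and met by examining the feet or referring the patient. Table 1 gives its performance in iQuaD as "Received by 91% of patients (via patient survey"). The other five rows of Table 1 range from 40% to 73%. The Discussion says that "foot examination was previously shown to be performed at a relatively high (though not optimal) rate" and that improvement may be harder to show, but that change is still expected. It gives no detectable difference for this outcome, and the power statement carries no exception for it.

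**The concern.** A single generic calculation is applied to six outcomes with very different starting rates. Centring it on 50% is conservative for the variance at a fixed difference, but it does not make a 15-point difference attainable where the starting rate leaves less room. At 91% there are only 9 points left, so the stated power describes an event that cannot happen for that outcome.

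Foot examination counts as much as any other behaviour towards the rule that a positive trial shows benefit on at least two of six. A reader who takes the statement at face value would credit a null foot result with nearly 84% power, or 89-92% at the larger cluster size, without knowing which gains the trial could detect there.

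**Working it through.** **Inputs.** From Sample size: 22 practices per arm, ICC 0.06, 5% significance, 42.5% versus 57.5%, 20 or 40 patients per practice. Sidedness is not stated. I take two-sided, in line with the Multiple comparisons section ("The 95% confidence interval corresponds to a type 1 error rate of 5" per cent). From Table 1: 91% for foot examination.

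**1. The plan's own figure.** Effective n per arm = k·m / (1 + (m − 1)·ICC). For k = 22 and m = 20 the design effect is 2.14 and n = 440/2.14 = 205.6. The Fleiss continuity correction gives n0 = (n·d − 1)² / (n·d²) = (30.84 − 1)² / 4.626 = 192.5. Then, with p̄ the mean of the two rates:

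Power = Φ{[d√n0 − 1.96√(2p̄q̄)] / √(p1q1 + p2q2)} = Φ{(2.081 − 1.386)/0.699} = Φ(0.994) = 84.0%, against 83.9% stated.

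| Practices per arm × patients | Stated | Corrected | Uncorrected |
|---|---|---|---|
| 20 × 20 | 80% | 80.1% | 82.9% |
| 22 × 20 | 83.9% | 84.0% | 86.3% |
| 20 × 40 | 89% | 89.4% | 91.0% |
| 22 × 40 | 92% | 92.1% | 93.3% |

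All four stated figures reproduce with the correction.

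**2. Room for 15 points.** For foot examination 91 + 15 = 106%, which cannot occur. The maximum gain is 100 − 91 = 9 points, and 15 points needs a control rate of at most 100 − 15 = 85%. The other Table 1 rates (40, 51, 59, 68 and 73%) all have room. At 22 × 20, uncorrected power for +15 points from those rates is 86, 87, 90, 95 and 97%, so the plan's figure is conservative for them.

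**3. What the trial could detect from 91%.** The documents give no mean register size, so m is an assumption. I use the plan's 20 and 40, plus 100 and 300, because all registered type 2 patients count for this outcome.

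Gain needed for 80% power, with 22 practices per arm:

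| Patients per practice | Uncorrected | Corrected |
|---|---|---|
| 20 | 6.4 points | 6.8 points |
| 40 | 5.8 | 6.1 |
| 100 | 5.4 | 5.7 |
| 300 | 5.2 | 5.4 |

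Power by gain, using Φ(d/SE − 1.96) with SE = √[(p1q1 + p2q2)/n] and no correction. Effective n per arm is 2200/6.94 = 317.0 at m = 100 and 6600/18.94 = 348.5 at m = 300:

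| Gain | m = 100 | m = 300 |
|---|---|---|
| 3 points | 30% | 33% |
| 4 points | 51% | 55% |
| 5 points | 73% | 77% |
| 6 points | 89% | 92% |

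For example, 91% to 95% at m = 100: SE = √[(0.0819 + 0.0475)/317.0] = 0.0202, and Φ(0.04/0.0202 − 1.96) = 51%. At m = 100, gains of 7, 8 and 9 points have 97%, 99.7% and about 100% power. The continuity correction lowers these values; for 4 points at m = 100 it gives 44%.

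**The case against.** The strongest reply is that 91% is not this trial's baseline. It is a patient-survey rate from an earlier UK-wide study, whereas the trial uses computer records in the North East and counts referral as well as examination. No computer-record rate is given. If the control rate proves to be 85% or lower, a 15-point gain is possible and the plan's figure is conservative: 70% to 85% has about 96% power at 20 patients per practice. This stands, and it makes the impossibility conditional. It does not rescue the unqualified statement, because 91% is the only figure the document offers.

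It is also fair to say that the Discussion warns about the high rate, and that each behaviour gets a 95% confidence interval, so an imprecise null would be visible. Both soften the consequence, but neither changes the stated power.

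Three stronger readings are tempting and are not supported:

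- A reader might infer that 83.9% is miscalculated. It reproduces; only its scope is wrong.
- A reader might infer that foot examination has little power for most possible gains. At 100 patients per practice, five of the nine whole-point gains (5 to 9 points) have 73% power or more. Variance is lower near 91%, and all registered patients count.
- A reader might infer that the two-of-six rule in effect rests on the other five behaviours. That would need a small true effect on foot examination, together with a register size and a foot-specific ICC that the documents do not give.

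**Conclusion.** The point holds as a matter of scope. The 83.9% is correct for 42.5% versus 57.5% but cannot cover foot examination at 91%, where no more than 9 points can be gained. For that outcome 80% power corresponds to a gain of about 5 to 6.5 points (about 5.2 to 5.4 at 100 to 300 patients per practice), or roughly 0.2 to 0.4 points more under the plan's continuity-corrected convention. Power falls to about half at 4 points and to about a third or less at 3.

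This rests on a 91% control rate, an ICC of 0.06 that is not stated specifically for foot examination, equal cluster sizes, assumed register sizes and a two-sided 5% test. The contradiction itself needs only a control rate above 85%. Severity is moderate: one stated power is too wide for one of six primary outcomes, and the design is unaffected.

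**What to change.** In the Sample size section:

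1. Limit the 15-point power statement to the five behaviours whose Table 1 rates (40-73%) leave room for it.
2. Add one line for foot examination: from 91%, with 22 practices per arm and ICC 0.06, 80% power needs a gain of about 5 to 6.5 points across 20 to 300 patients per practice. At 100 to 300 patients, power is about 50-55% for 4 points and 30-33% for 3. State the assumed register size and whether a continuity correction is used.
3. Say that 91% is a survey rate from the earlier study while the trial outcome comes from computer records, so the starting rate is an assumption.

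The line cannot wait for the trial's own pre-intervention rate, because the 24-month extract is taken only after month 12. Nor should it claim a gain from baseline adjustment, since the Main trial analysis section plans baseline-rate covariates only for the two prescribing behaviours.

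The cost is a change of wording and one extra power line. Recruitment, the primary analysis and the two-of-six rule do not change; the stated power becomes less favourable for one outcome.
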